### Training of Study Teams

The study investigators provided extensive training to the field teams regarding their assigned tasks. All staff received training on good clinical practice, and the pregnancy surveillance and birth notification teams received training on survey procedures and appropriate documentation. The implementation team received comprehensive training on the KMC package, implementation, and counseling; they were also trained on screening and recruitment procedures and referral protocols.

The data collection team was trained on interviewing techniques and data documentation using a handheld device. The training also included newborn examinations, recognizing symptoms of disease, prompt referrals, ascertaining KMC compliance, breastfeeding practices, and anthropometric measurements using the standard methodology and standardization processes [33]. The team was also trained to calibrate anthropometric instruments regularly using the standard measurement rods and weights.

The LHWs are the frontline health workers in the public sector employed by the Ministry of Health. The LHWs in the intervention clusters received orientation on the KMC intervention and standard essential newborn care. In contrast, LHWs in the control clusters were trained on standard essential newborn care only.

### Data Management

A data collection application was developed to collect the data on recruitment and outcome measures during follow-ups. These applications have a built-in range and consistency checks. If there are specific queries, the data is returned to the respective teams, and the query is resolved within 48 hours of data collection. The data are transferred to the Aga Khan University (AKU) secure data servers at the data management unit daily. A trial flow was developed, detailing the number of participants through assessments of eligibility, randomization, follow-up, and analysis. Reasons for exclusions and withdrawals are appropriately explained and documented.

### Data Analysis

For data analysis, we will use the intention to treat approach using STATA software (version 17; StataCorp). Data will first be analyzed using person-time as the denominator for the primary outcome (neonatal mortality between enrollment and 28 days of age). Hazard ratios and 95% CIs will then be calculated using a Cox regression model to evaluate the effect of the intervention (cKMC) on infant deaths. We will also estimate the impact of cKMC using the number of enrolled infants as the denominator to deduce risk ratios using generalized linear models of the binomial family with a log link function. The summary data for background characteristics in the intervention and control groups will be presented as means and proportions.

The effect of KMC on secondary outcomes (ie, exclusive breastfeeding, weight and length gain, the incidence of illnesses and hospitalizations, and care-seeking behavior) will be assessed using linear or logistic regression after adjusting for clustering in the case of twins or another enrolled baby subsequently born to the same mother, as well as other potential confounders.

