## Methods

### Study Design

We are conducting a cluster randomized controlled trial in one of the rural districts of Pakistan. The cKMC package has been developed based on preliminary research, involving in-depth interviews and focused group discussions with major stakeholders. A conceptual framework was developed based on the existing data to guide research themes (Figure 1).

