#### Sample Size

We considered union councils in the talukas as the clusters for our trial. The union council comprised a population of 25,000, with expected 29 births per 1000 people. We anticipated 200 LBW births per cluster, given the 27.7% prevalence of LBW in the study area [30]. Literature suggests 13.3% of the LBW infants die in the neonatal stage [31]. With an expected 30% reduction in mortality, 12 clusters (union councils) were needed per arm (a total of 24 clusters for the trial) to achieve 90% power and a 5% significance level. We estimated 200 births with a birth weight of less than 2.5 kg per cluster. A total of 4800 participants in the intervention and control groups are required to complete the study.

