**Figure 2 figure2:**
[figure not shown]
Study site and selected clusters. UC: union councils.

The clusters (union councils) were randomized using a restricted randomization scheme using the following indicators: population, live birth, the prevalence of LBW, neonatal mortality, skin-to-skin contact, breastfeeding practices, and distance from the taluka hospital. We conducted a baseline survey of the study area to collect data on these indicators. Blinding is not possible because of the nature of the intervention; however, to minimize measurement bias on the effect of the intervention, the data collection team is independent of the implementation team.

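### The stated analysis allows for clustering within mothers only (secondary outcomes) and nowhere for the 24 randomised union councils

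*Protocol article*

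**What the plan says.** The design is clustered throughout. Under Study Design: "We are conducting a cluster randomized controlled trial in one of the rural districts of Pakistan". Under Sample Size: "We considered union councils in the talukas as the clusters for our trial", with 12 per arm, 24 in all, about 200 low-birthweight infants in each and 4800 in total, "to achieve 90% power and a 5% significance level". Under Randomization: "The clusters (union councils) were randomized using a restricted randomization scheme".

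The Data Analysis section then sets out the models:

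- **Primary outcome, hazard ratio:** "Hazard ratios and 95% CIs will then be calculated using a Cox regression model". No frailty term, cluster-robust variance or other allowance is given.
- **Primary outcome, risk ratio:** "generalized linear models of the binomial family with a log link function", again with no allowance.
- **Secondary outcomes:** linear or logistic regression, "adjusting for clustering in the case of twins or another enrolled baby subsequently born to the same mother", together with potential confounders.

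The Abstract repeats the Cox, linear and logistic models without a cluster term. Nothing else in the article says that the analysis accounts for union council.

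**The concern.** In a cluster randomised trial, the variance of the treatment effect comes from variation between the randomised units as well as between infants. A model that treats infants as independent omits the first part. The section does discuss clustering, but the only level it names is not the randomised one. Adjusting for mothers cannot stand in for adjusting for councils: a mother contributes one or two infants in most cases, a council about 200.

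The article itself gives reasons to expect infants of one council to resemble each other. Allocation was restricted on baseline council-level mortality, low-birthweight prevalence, skin-to-skin contact, breastfeeding and distance from hospital. Each council has its own basic health unit (Study Site). Each cluster has its own pair of data collectors (Data Collection), so measurement habits are shared within a council too. The primary mortality test, which is meant to inform national policy, is at stake, as are the secondary comparisons.

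**Working it through.** **Inputs from Sample Size.** Control mortality 13.3%; 30% relative reduction, so 0.133 × 0.7 = 9.31%; 90% power; 5% level (two-sided assumed, since the article does not say); m = 200 per cluster; 12 clusters per arm. No ICC, between-cluster coefficient of variation k or design effect is stated.

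**Step 1. The plan's own figures.** 25,000 × 0.029 × 0.277 = 200.8 low-birthweight births per council, and 24 × 200 = 4800. Both reproduce.

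**Step 2. Size without clustering.** With (1.960 + 1.282)² = 10.507:

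n per arm = 10.507 × (0.133 × 0.867 + 0.0931 × 0.9069) / (0.0399)² = 10.507 × 0.19974 / 0.001592 = 1318

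The pooled-variance version gives 1322. Either is about 7 councils per arm (1318 / 200 = 6.6). The plan has 2400 per arm, a ratio of 2400 / 1318 = 1.82.

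**Step 3. Between-council variation that would explain 12 per arm.** The Hayes–Bennett formula is

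c = 1 + 10.507 × [0.19974 / 200 + k²(0.133² + 0.0931²)] / 0.0399²

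Setting c = 12 gives k = 0.159. Then ICC = k² × p / (1 − p) = 0.0253 × 0.133 / 0.867 = 0.0039, and the design effect is DE = 1 + 199 × 0.0039 = 1.78. This agrees with the ratio in Step 2.

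**Step 4. Effect of ignoring union council.** A naive standard error is too small by the factor 1/√DE. At DE = 1.78 that is 0.75, so 25% too small, and the correct interval is √1.78 = 1.33 times as wide. The true two-sided error at nominal 5% is 2 × [1 − Φ(1.96 / √DE)]:

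| ICC (m = 200) | DE | True type I error |
|---|---|---|
| 0.001 (assumed) | 1.20 | 7.3% |
| 0.003 (assumed) | 1.60 | 12.1% |
| 0.0039 (implied by the planned size) | 1.78 | about 14% |
| 0.005 (assumed) | 2.00 | 16.5% |
| 0.01 (assumed) | 2.99 | 25.7% |

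For secondary outcomes with about 200 infants per council, assumed ICCs of 0.01 to 0.05 give about 26% to 55% by the same formula.

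**Step 5. Check by simulation.** Beta-binomial data with no true effect (24 clusters of 200, 13.3% mortality, unrestricted allocation, 20,000 runs) gave naive error rates of 7.5%, 12.1%, 16.2% and 25.4% at ICC 0.001, 0.003, 0.005 and 0.01. A t-test on the 24 cluster proportions kept 4.9% to 5.0% at each.

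**The case against.** The strongest reply is that this is condensed reporting. The mother-level clause sits in the sentence on secondary outcomes; for mortality the article is silent on variance estimation, which an article may leave to the full protocol or analysis plan. The clause could also describe a further level of correlation on top of a cluster analysis taken for granted, and a sample size that seems to allow for council variation suggests the investigators had it in mind.

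Part of this stands. The wrong-level statement strictly concerns the secondary outcomes; for mortality the fault is that two models are specified with no allowance at any level. An unseen analysis plan may already deal with both. But the section does take up clustering, and the only level it names is not the randomised one, so a reader following it would fit the wrong models.

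The objections to the size also have force:

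- The implied design effect is back-calculated. If part of the excess over 1320 per arm were an unstated attrition margin of 10% or 20% (an illustration), it would fall to about 1.64 or 1.45 and the error to about 12.5% or 10%.
- Restricted allocation reduces chance imbalance between arms where the baseline indicators predict outcome, so the unrestricted simulation may overstate the inflation.
- Neurodevelopment is assessed in a subset, so clusters are smaller there and the inflation is less.

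These points change the amount of inflation. They do not make an analysis that omits union council valid.

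**Conclusion.** The point holds and should be corrected before the analysis. As written, the primary models ignore clustering and the secondary models adjust for the wrong level alone. If the text is followed and the ICC is above zero, intervals are too narrow and P values too small. At the variation implied by the planned size (k about 0.16, ICC about 0.004, DE about 1.8), the mortality test has a type I error near 14%; even at an ICC of 0.001 it is about 7%. These figures assume a two-sided 5% test, 200 infants per cluster and no benefit from the restricted allocation. The ICC is inferred or assumed, because the article states none. The plan is also inconsistent with itself: 2400 per arm against about 1320 under individual randomisation fits an allowance for council variation that the stated analysis does not carry through.

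**What to change.** State in Data Analysis, and in the analysis plan if it does not already say so, that every primary and secondary model accounts for union council as the top-level cluster, with mothers nested within it. Suitable choices are:

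- **Hazard ratio:** Cox model with shared frailty by union council, or cluster-robust variance by union council.
- **Risk ratio and secondary outcomes:** mixed models or generalised estimating equations by union council.
- **Small number of clusters:** a t reference with 24 − 2 = 22 degrees of freedom or a bias-corrected sandwich variance.
- **Confirmation:** a cluster-level t-test, or a permutation test over the allocations that the restricted scheme permitted.

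The first two items are essential. The exact small-sample method may be left to the analysis plan, provided one is named before the data are analysed.

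The cost is a change of wording and of options in the Stata commands. No new data and no change to conduct are needed, and the article reports that the analyses are not yet complete. Intervals will be wider, as they should be.

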### Monitoring and Evaluation

The study investigators and technical staff from the AKU will interact with the study team through regular field site visits to review the study process and progress. The study managers will share weekly reports. All key areas will be monitored, including the enrollment rate, timing of the intervention delivery initiation, consent procedures, referrals and follow-up visits, and timely transmission of data to AKU.

## Results

The Ethics Review Committee of Aga Khan University, Pakistan, approved the study protocol on February 15, 2017 (ID. 4467-Ped-ERC-16). In addition, ethical clearance was sought from the National Bioethics Committee, Pakistan. The trial is registered with clinicaltrials.gov: NCT03545204. Data collection began in August 2019 and will be completed in December 2021. Data analyses are yet to be completed. The datasets used for the article and the study is available from the corresponding author on request.

## Discussion

Despite the robust evidence supporting the use of KMC for preterm and LBW survival, scaling-up of KMC has proven an elusive goal for Pakistan and other low-income and middle-income countries for the last 40 years [34]. However, with increased awareness concerning the magnitude of newborn mortality among preterm and LBW infants, our trial anticipates providing evidence on the impact of initiating cKMC in the remote areas of Pakistan, where incubator care is inaccessible. Moreover, the benefits of performing KMC in the community setting will also be emphasized, facilitating the much-needed uptake of this intervention within rural communities.

Most of the evidence that favors KMC is derived from hospital-based settings; however, a recent study concluded that cKMC substantially improves neonatal and infant survival in low-income countries. KMC in community settings for infants with LBW could substantially reduce neonatal and infant mortality [18]. Furthermore, research carried out in Haryana, India, proposed cKMC was feasible and acceptable, with high adoption rates observed in mothers of LBW babies [35]. Similarly, a study conducted in Pakistan demonstrated that a package of interventions that included essential newborn care, chlorhexidine, and KMC reduced the risk of neonatal infection and omphalitis and positively impacted weight gain [19]. Although there is some evidence in favor of cKMC in low-income countries, it is imperative to conduct robust research on the impact of cKMC in Pakistan for its large-scale implementation.

There is a need to adopt community-based KMC in Pakistan’s rural areas, where most deliveries occur at home [3]. Our preliminary research showed a high acceptance rate of KMC in a community setting, with a willingness to perform KMC for at least 8 hours at home with family support. However, community mobilization was critical to resolve barriers and to achieve acceptance rates within the community. We are also focusing on pregnancy surveillance through which pregnant women are identified via door-to-door surveillance, and newborns are identified by an early birth notification system and follow-up at home. In addition, well-trained community health workers such as KMC champions carry out regular sessions in the community to develop mother and father champions and sensitize the community. Besides KMC champions, we intend to see the effectiveness of community KMC on neonatal mortality in LBW babies by engaging the LHW program through this study. The LHW program in rural Pakistan is the backbone of primary health care, including maternal and child health, and covers approximately 60% of the rural population [36].

Although there is considerable evidence on the effectiveness of KMC, previous trials were conducted in a controlled environment, where the results cannot be generalized to programs operating under field conditions. The objective of our trial is to scale up KMC practice in the remote areas of Pakistan and test this model, which can then be delivered by the health care providers employed in the public sector such as LHWs, lady health supervisors, community midwives, and lady health visitors. The findings of this study will provide enough evidence to develop policies and programs aimed at preventing neonatal mortality and improving maternal and child health and growth outcomes in poor resource settings.

cKMC intervention may be effective in preventing sepsis and subsequently improve survival in LBW newborns in Pakistan and other low-income and middle-income countries worldwide.

## Abbreviations

AKU: Aga Khan University
BHU: basic health unit
cKMC: community kangaroo mother care
IEC: information, education, and communication
KMC: kangaroo mother care
LBW: low birthweight
PSBI: possible serious bacterial infection
LHW: lady health worker
